### Data collection

Data sources will consist of (1) participant surveys, (2) SP surveys, (3) external rater assessments of SP encounter video recordings, and (4) virtual interviews with participants. All surveys will be completed on-line through SurveyMonkey [44] for SPs and external raters, and the Moodle learning management system for participants. All virtual workshop activities will be hosted using the Zoom Video communications platform [45] and coordinated through the research team.

Participant and SP completed measures will be collected at four time points: at baseline (i.e., prior to intervention), upon intervention group completion of the program (within 8 weeks after completion), upon control group completion of the intervention (within 8 weeks after completion), and at six months following the intervention. Participants will be asked to sign up for a virtual SP encounter at each data collection point. The initial SP encounter must be completed before the participant gains access to the ABCs curriculum on Moodle. The next module in sequence will only be released after completion of the previous module. Each SP encounter will occur online through Zoom and will be video recorded. A clinical scenario will be provided in advance, and a SP will simulate the encounter. The same clinical scenario will be used for all simulated encounters. Virtual encounters will be capped at 20 min. No immediate feedback will be provided to participants.

The video recordings will be reviewed and rated asynchronously by trained raters. These raters are interdisciplinary HCPs (e.g., physicians, nurses, psychologists, social workers) who are trained to provide education in serious illness communication to clinician learners. Raters will also be trained to use the rating scale (ACE-CT), given a rating manual, and will be engaged in a virtual calibration session. Raters will be blinded to the training condition (control/intervention conditions) and to the data collection time-point. Raters are not involved in the delivery of the interactive workshops. All video recorded encounters from a participant will be independently assessed by a randomly assigned rater, with 15% duplication between raters to test for consistency in ratings.

Select participants will be asked to participate in qualitative data collection at Follow up 3. Purposive sampling will be used to ensure a diversity in participants and perspectives. We will complete qualitative interviews with 15 to 25 selected participants, or until thematic saturation is reached. All identifying information will be removed from data once collected, with use of unique coded identifiers to maintain participant anonymity. All study data will be password-protected and maintained on McMaster University servers.

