**Fig. 1 Fig1:**
[figure not shown]
Diagram of ABCs program components

**Table 1 Tab1:** The ABC program’s educational strategies and components

Conceptual Framework
• Use of a conceptual framework that clarifies serious illness communication concepts. • Use of a framework that draws from strengths of existing programs but focuses on specific skills that are relevant to learners and clinicians at all training and practice levels, as well as across all disciplines, specialties, and care settings. • Use of a framework grounded in person-centeredness and competency.
Modules
• Asynchronous videos to support development of micro-skills, featuring example encounters with SPs and experts.
Workshops
• Online synchronous sessions featuring case scenarios and simulated encounters with SPs to put concepts into practice and refine communication skills.
Coaching
• Opportunities for experts to observe communication and provide advice through simulated practice.
Personal reflection
• Reflection encouraged following each module and workshop.
Learning management system (LMS)
• A custom Moodle-based LMS that allows participants to easily access online materials, book their SP encounter sessions, and complete study surveys.
Duration
• A three-month long training program which provides sufficient time to gain knowledge, practice skills, reflect on learning, and potentially change behaviour in real clinical contexts.

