#### Primary outcomes

The primary outcome for this study is the validated Assessment of Clinical Encounter-Communications Tool (ACE-CT) which external expert raters will used to evaluate the quality of participant communication with SPs in the virtual simulated encounters (Table 2) [37]. The ACE-CT is comprised of 14 items and was developed through a rigorous 3-phase multi-methods process. Through our pilot study, psychometric properties of the ACE-CT were assessed, indicating that the tool has high internal consistency (Cronbach’s ⍺=0.96), moderate inter-rater and intra-rater reliability, and sound content and construct validity.

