### Statistical power/sample size

The primary analysis will be a linear regression analysis, where the outcome variable is the ACE-CT score at Follow-up 1, and covariates are the baseline ACE-CT score, stratification variables, and intervention arm. If the intervention arm covariate is statistically significant, then the intervention will be deemed as statistically significant. However, for accurate sample size estimation for such a regression analysis, one would need not only the hypothesized change in ACE-CT scores from pre to post intervention, but also the estimated correlation for all the stratification factors and the distribution of personnel across factors. As these estimates are unlikely to be accurate, a simplified sample size estimate can be generated by assuming a two-sample t-test and adding an inflation factor. Hence, using data from our pilot study [37], it is estimated that the pre-intervention global mean for ACE-CT is 2.90 (standard deviation [SD] = 0.73), the post-intervention global mean for ACE-CT is 3.45 (SD = 0.78) and the mean change from pre- to post-intervention is 0.54 (SD = 0.75) amongst individuals undergoing the ABCs program. It is assumed there will be no change in the post-intervention global mean for ACE-CT amongst individuals who do not receive the program. Based on these assumptions, a two-sided, two-sample equal variance t-test (alpha = 0.05) will achieve 90% power with 42 HCPs per arm (84 total). To account for the different analytic method use, potential overestimation of the hypothesized effect, and to account for potential non-completion by an estimated 20% of HCPs, the target sample size will be doubled to 168.

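### The primary ACE-CT regression omits rater, which costs precision but not validity; blinding and workshop separation are stated for raters but not for the standardized patients who score secondary outcomes

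*Protocol article*

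**What the plan says.** **Rating.** Under Data collection: "All video recorded encounters from a participant will be independently assessed by a randomly assigned rater, with 15% duplication between raters". The stated purpose of the duplication is to check rating consistency; the article does not say whether second ratings enter the analysis. Raters are trained, calibrated, and blinded to condition and time-point. Also: "Raters are not involved in the delivery of the interactive workshops". Under Primary outcomes, the tool is credited with "moderate inter-rater and intra-rater reliability"; no coefficient is given.

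**Primary model.** Under Statistical power/sample size, the outcome is ACE-CT at Follow-up 1 and the "covariates are the baseline ACE-CT score, stratification variables, and intervention arm". Significance of the arm term decides the result. Data analysis adds multilevel mixed models over time without naming their levels.

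**SP-scored measures.** Table 2 lists three: selected QQPPI items, selected Feeling Heard and Understood items, and a one-item global rating. The SP who played the encounter completes them. Table 1 describes the workshops as "Online synchronous sessions featuring case scenarios and simulated encounters with SPs to put concepts into practice and refine communication skills". By the Study design section, controls start the program only after Follow-up 1. The article makes no statement on SP blinding, on how SPs are allocated to encounters, or on keeping scoring SPs out of workshops.

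**The concern.** With moderate agreement between raters, part of the spread in ACE-CT reflects who scored the video. The study assigns the raters, so this source of variance can be recorded and modelled. A regression without it leaves that variance in the residual and widens the confidence interval for the arm effect. The sample-size section itself allows for an overestimated effect, and precision matters most if the true effect is smaller than planned.

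The SP gap is of another kind. An SP who had practised with a participant in a workshop would know that participant's arm when scoring Follow-up 1. The article guards against this for raters, so the risk was recognised, but it states no equivalent for the other group of outcome assessors.

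**Working it through.** **1. The plan's own figure.** Inputs from Statistical power/sample size: difference 0.54, SD 0.75, two-sided alpha 0.05, 90% power, and for controls "It is assumed there will be no change in the post-intervention global mean for ACE-CT amongst individuals who do not receive the program". With 42 per arm the noncentrality is 0.54 / (0.75 × √(2/42)) = 3.30, and exact power is 90.3%. The stated 42 per arm reproduces. After 20% loss from 168, 168 × 0.8 = 134.4, or about 67 per arm, with 98.5% power by the same t-test.

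**2. What the pilot SDs imply.** SDs are 0.73 (pre), 0.78 (post) and 0.75 (change).
- Covariance = (0.73² + 0.78² − 0.75²)/2 = 0.2894
- Correlation = 0.2894/(0.73 × 0.78) = 0.508
- Slope on baseline = 0.2894/0.73² = 0.543
- Residual variance = 0.78² − 0.2894²/0.73² = 0.451

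With the same rater at both visits, baseline adjustment removes about 54% of a rater's severity and leaves about 46%.

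**3. Same rater at both visits.** Let rater severity be a share s of score variance (assumed), V = s × 0.73 × 0.78. With rater removed, residual variance = (0.78² − V) − (0.2894 − V)²/(0.73² − V).

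| Share s | Residual variance | Reduction |
|---|---|---|
| 10% | 0.438 | 3% |
| 20% | 0.421 | 7% |
| 30% | 0.399 | 12% |
| 40% | 0.368 | 18% |

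This shows the potential gain before the cost of estimating rater effects. Simulation at 67 per arm, with 5 or 10 raters assumed and variance components treated as known, gives these changes in arm-effect variance over shares of 10% to 40%:
- random rater effect: a cut of about 3% to 16%
- fixed rater terms: from about 3% worse to 14% better

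With 15 raters, fixed terms made it worse by 8%, 6% and 2% at shares of 10%, 20% and 30%.

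**4. Different raters at the two visits.** Simulation with 67 per arm, 10 raters, SD 0.75, correlation 0.5 for the non-rater part, and fixed rater terms for both visits:

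| Share | SE without rater | SE with rater | Power at 0.27 without | Power at 0.27 with |
|---|---|---|---|---|
| 10% | 0.120 | 0.118 | 65% | 63% |
| 20% | 0.121 | 0.112 | 62% | 69% |
| 30% | 0.116 | 0.102 | 61% | 73% |
| 40% | 0.120 | 0.097 | 60% | 81% |

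The SE without rater is about 2% to 24% larger. At a 10% share there is no clear gain. The effect 0.27 is half the planned 0.54.

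**5. Validity without a rater term.** Across both assignment patterns the mean estimate was 0.53 to 0.54 for a true 0.54, type I error was 4% to 6%, and power at 0.54 was 99% or more.

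**6. SP-scored outcomes.** The article gives no size for any effect of knowing the arm. For illustration, if it shifted scores by 0.1, 0.2, 0.3 or 0.5 SD, a t-test at 67 per arm with no true effect would be significant with probability 9%, 21%, 41% or 82%.

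**The case against.** The strongest reply is that the primary analysis is sound as it stands. Raters are randomly assigned and blinded, so scores sharing a rater do not distort the test, and step 5 confirms this. Power at the planned effect is ample, the sample size was doubled partly to allow for the different analysis, and the pilot SD presumably already contains rater noise. If one rater scores all of a participant's videos, baseline adjustment absorbs part of rater severity. Fixed rater terms then gain almost nothing: in a simulation with ten raters, the SE was 0.106 without and 0.108 with them at a 10% share, and 0.093 against 0.091 at 40%.

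Most of this stands. It rules out fixed terms as the general remedy and limits the point to precision. It does not remove the case for a random rater effect, which improved precision at every share examined. Nor is this detail left to an analysis plan, because the article lists the primary model's covariates.

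On SPs, the reply is that the article is only silent: it does not say that workshop SPs also score assessments or know the arm, and a fuller protocol may settle it. That is right, and it makes this a risk. Still, the article states the safeguards for one group of assessors and not for the other.

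**Conclusion.** The point holds as a precision loss in the primary analysis and an unaddressed risk in the SP-scored secondary outcomes. With one rater per participant, a random rater effect would cut arm-effect variance by roughly 3% to 16%. This rests on assumed rater shares of 10% to 40%, 5 or 10 raters and known variance components; none of these is in the article. The gain is larger if raters differ between visits, and the sentence on rater assignment could be read either way.

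Four stronger readings are tempting but unsupported:
- That every outcome depends on a rater or SP. SE-12, EPCS and BLUE-Q are self-reported.
- That the primary estimate is biased or its type I error inflated. Blinded random assignment prevents this.
- That the sample size is too small. The stated figure reproduces, and power at 0.54 is high throughout.
- That SP scores are biased toward the program. This would require scoring SPs to know the arm, which the article does not say.

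The omission of rater is shown for the primary regression only, since the multilevel models do not name their levels.

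**What to change.** 1. State whether one rater scores all of a participant's videos or each video is assigned separately.
2. Analyse ACE-CT in a mixed model with the stated covariates and rater as a random effect. Include both ratings of each duplicated video, with a participant random effect to link them. Avoid fixed rater terms, which can lose precision with many raters and a small rater share.
3. Add SP as a random effect for QQPPI, Feeling Heard and Understood and the global rating, and state how SPs are allocated to encounters.
4. Apply the raters' rule to scoring SPs: no workshop role with that wave's participants, and not told arm or visit. If this cannot be arranged, report the SP-scored outcomes as potentially unblinded.

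The cost is keeping rater and SP identity with each score, slightly more complex modelling, and some SP scheduling. With waves planned for 2025, 2027 and 2029, the SP rule can still be adopted for any wave not yet run.

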### Data analysis

The intervention and unit of analysis will be at the individual level. Descriptive statistics (i.e., means, standard deviations, and frequencies) will summarize recruitment, population demographics, and adherence to study procedures. Participant characteristics (e.g., province, prior training, etc.) will be tabulated. Regression analyses will be conducted to analyze relationships between independent variables and outcomes, and to compare group means across different levels of categorical variables. Multilevel mixed models with repeated measures will also be used to investigate the effect of the intervention over time (baseline, follow-up 1, 2, and 3). Correlations between participant, SP, and rater responses to the respective outcome scales will be performed using Pearson’s coefficient. Interview audio files will be transcribed verbatim and reviewed for accuracy. Thematic analysis guided by Braun and Clarke’s framework [46] will be conducted independently by two researchers to identify key aspects of participants’ experiences, with core themes developed through group discussion. NVIVO software will be used for qualitative data management.

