The program adopts a 3-month long online blended learning format (i.e., participants engage in five asynchronous online modules and three synchronous interactive workshops) that provide any clinician (regardless of discipline, specialty, or years in practice) with practical tools, tips, and strategies to implement when communicating with seriously ill patients and their families. We piloted this education program with medical learners and interdisciplinary HCPs [32, 33] and found that completion of the ABCs program improved their self-reported confidence in initiating conversations around serious illness, as well as competency in serious illness communication, as evaluated by external raters. The ABCs program will be accessed via abcseducation.ca, a custom Moodle learning management system which is hosted, developed, and supported by Lingel Learning (i.e., a Moodle certified partner and service provider). Figure 1 shows the program components and organization. Table 1 further describes each of these components.

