### Study design

We will conduct a prospective stepped-wedge randomized controlled trial [34] of interprofessional health care providers (HCPs) who enroll in the ABCs program. This stepped-wedge trial will consist of up to three waves of enrolment (first wave in 2025; second in 2027; and a third in 2029). At the start of each wave, all participants that meet eligibility criteria will complete baseline measures. Following this, participants will be randomized to an intervention or a control group. The intervention group will have immediate access to the ABCs program, whereas the control group will have to wait until the intervention group completes the program before they can receive the training. Once the intervention group completes the program, and before the control group begins the program, all study participants will complete follow-up assessments (Follow-up 1). Assessments at Follow-up 1 will serve as the primary outcome measures for this study. All study participants will complete another round of follow-up assessments once the second group completes the program (Follow-up 2). A subset of the participants will also complete a final follow-up 6 months after the cross-over group completes their training (Follow-up 3). Assessments at Follow-ups 2 and 3 will serve as secondary outcome measures for this study. See Fig. 2 for a depiction of the study design’s first wave, which will be repeated at the second and third waves. Ethical approval for this study was obtained from the Hamilton Integrated Research Ethics Board (#17801). See https://clinicaltrials.gov/study/NCT06606470 for the approved operating protocol. The SPIRIT-Outcomes 2022 checklist was corroborated when drafting this protocol (see supplementary material).

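### The intervention is called individual-level, yet the trained arm shares live workshops and coaches by Follow-up 1, and the primary regression has no term for that sharing

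*Protocol article*

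**What the plan says.** The Data analysis section of the protocol article sets the level of the trial: "The intervention and unit of analysis will be at the individual level". The program description says that "participants engage in five asynchronous online modules and three synchronous interactive workshops". Table 1 describes the workshops as "Online synchronous sessions featuring case scenarios and simulated encounters with SPs to put concepts into practice" and lists coaching as a separate component: "Opportunities for experts to observe communication and provide advice through simulated practice".

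The Statistical power/sample size section fixes the primary model: "The primary analysis will be a linear regression analysis, where the outcome variable is the ACE-CT score at Follow-up 1", and its "covariates are the baseline ACE-CT score, stratification variables, and intervention arm". Workshop, facilitator and cohort are not among them.

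The Study design section places the primary time point before controls are trained: "Once the intervention group completes the program, and before the control group begins the program, all study participants will complete follow-up assessments". The Data analysis section adds: "Multilevel mixed models with repeated measures will also be used to investigate the effect of the intervention over time". That model supplements the primary regression, and the article names no workshop level for it.

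**The concern.** Randomising individuals does not make their outcomes independent once some of them are taught together. At Follow-up 1, trained participants have shared live sessions and coaches, while controls have had none. The design is therefore individually randomised with clustering in one arm only, usually called partially nested. The shared part is not marginal: the Discussion names simulated practice and expert feedback among the elements expected to change behaviour.

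If sharing a workshop or facilitator makes scores more alike, a regression with independent residuals underestimates the variance of the trained-arm mean. The confidence interval for the average program effect is then too narrow, and the test can reject too often. Enlarging the sample does not repair a wrong standard error. The doubling to 168 is in any case justified by the analytic method, possible overestimation of the effect, and non-completion, not by clustering.

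**Working it through.** **Inputs from the article (Statistical power/sample size).** Difference 0.54, SD 0.75, two-sided alpha 0.05, power 90%, 42 per arm, target 168, non-completion 20%. Analysed per arm: 168 × 0.8 / 2 = 67.2, taken as n = 67.

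**Inputs assumed, because the article gives none.** Workshop group size m = 6, 10 or 14, and ICC = 0.01, 0.05 or 0.10. Groups are taken as stable across the three workshops. Total SD is held at 0.75 in both arms, with no gain credited for baseline adjustment.

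**Step 1: the plan's own figure.** With independent observations, the exact noncentral t gives power 89.6% at 41 per arm and 90.3% at 42. The stated 42 reproduces. With 67 per arm, the 90%-power difference is 0.42.

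**Step 2: formulas.**
- Design effect, trained arm only: DE = 1 + (m − 1) × ICC.
- Naive SE = 0.75 × √(2/n); true SE = 0.75 × √((1 + DE)/n).
- Naive/true ratio = √(2/(1 + DE)).
- Actual two-sided error of the naive test = 2 × (1 − Φ(1.96 × ratio)).
- Satterthwaite df = (DE + 1)² / (DE²/(k − 1) + 1/(n − 1)), with k = n/m trained groups.
- 90%-power difference ≈ (t at 0.975 + t at 0.90, on that df) × true SE.

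**Step 3: one case in full (m = 14, ICC 0.05).** DE = 1 + 13 × 0.05 = 1.65. Naive SE = 0.75 × √(2/67) = 0.130; true SE = 0.75 × √(2.65/67) = 0.149; ratio 0.869. Error = 2 × (1 − Φ(1.703)) = 8.9%. With k = 67/14 = 4.8, df = 9.6, and the detectable difference is (2.242 + 1.377) × 0.149 = 0.54.

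**Step 4: the range.**

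| m | ICC | DE | Naive/true SE | Naive SE too small by | Actual error | df | 90%-power difference |
|---|---|---|---|---|---|---|---|
| 6 | 0.01 | 1.05 | 0.988 | 1% | 5.3% | 34.0 | 0.44 |
| 6 | 0.05 | 1.25 | 0.943 | 6% | 6.5% | 30.0 | 0.46 |
| 6 | 0.10 | 1.50 | 0.894 | 11% | 8.0% | 26.4 | 0.49 |
| 10 | 0.01 | 1.09 | 0.978 | 2% | 5.5% | 19.5 | 0.45 |
| 10 | 0.05 | 1.45 | 0.904 | 10% | 7.7% | 15.6 | 0.50 |
| 10 | 0.10 | 1.90 | 0.830 | 17% | 10.4% | 13.0 | 0.55 |
| 14 | 0.01 | 1.13 | 0.969 | 3% | 5.8% | 12.9 | 0.47 |
| 14 | 0.05 | 1.65 | 0.869 | 13% | 8.9% | 9.6 | 0.54 |
| 14 | 0.10 | 2.30 | 0.778 | 22% | 12.7% | 7.7 | 0.62 |

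The shortfall is expressed relative to the true SE. Simulation with five groups of 14 gave errors of 8.6% (ICC 0.05) and 12.8% (ICC 0.10), in line with the formula.

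**Step 5: an extreme layout.** If 84 per arm were spread over three waves with one workshop group per wave, m would be 28. At ICC 0.05, DE = 2.35, the ratio is 0.773 and the error about 13%. There would be at most three trained clusters, and their variance could barely be estimated.

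**The case against.** **The sentence has a milder reading.** The trial is called stepped-wedge, a label often used for cluster designs, so the sentence may only mean that people rather than sites are randomised and analysed. That is right for randomisation. It does not make the delivery individual, and the stated primary model still has no group term.

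**This may be left to the analysis plan.** Variance estimators and degrees of freedom often are, and the article fixes covariates rather than an estimator. But the article does more than stay silent: it asserts that the intervention is individual and names a model consistent with that.

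**The clustering is inferred.** This stands. The article gives no group size, number of facilitators or ICC, and does not say whether the same people stay together for all three workshops. With small groups and ICC near 0.01, the effect is negligible.

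**Error need not be inflated under every null.** This also stands. If the program affects nobody, shared workshops cannot create correlation, and individual randomisation keeps the ordinary test at 5%. The inflated rates apply when workshop effects vary around an average of zero. Interval width under a real effect is the more general concern.

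**Stronger readings the article does not support.** A reader might infer that residual variances differ between arms, but the only relevant SDs, 0.73 before and 0.78 after training in the pilot, are close. A reader might infer that a good facilitator would be mistaken for a program effect. Coaching is a listed component, so that depends partly on the estimand. A reader might also infer that the trial is underpowered. At a difference of 0.54, 90% power is kept in most of the range shown and lost only at ICC 0.10 with groups of 10 or more.

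**Conclusion.** The point holds conditionally. The article's description of delivery does not fit its statement that the intervention is individual, and the stated primary regression makes no allowance for shared workshops or facilitators. The direction is certain for any positive within-group correlation: the standard error of the average program effect is too small.

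The size rests on assumed group sizes and ICCs. It runs from trivial (1% too small; error 5.3%) to material (22% too small; error 12.7%), the error rates being those for a zero average effect with varying workshop effects. The fault lies in the precision claimed for the primary result, not in the randomisation or the sample size calculation, which reproduces. It should be corrected, but it does not undermine the design.

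**What to change.** 1. Reword the Data analysis sentence to say that randomisation is individual and delivery is partly in groups.
2. Record workshop group and facilitator for each participant at each session. This may be hard to reconstruct later, and the waves are planned from 2025 to 2029.
3. Keep the stated covariates in the primary model. Add a partially nested random effect for workshop group or facilitator in the trained arm, with controls as singletons, and use Satterthwaite or Kenward-Roger degrees of freedom.
4. If membership changes between workshops, define the cluster by facilitator or use a multiple-membership term.
5. If there are too few groups to estimate the variance, report the adjusted result as a sensitivity analysis and state that limit.

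**Cost.** Two recorded variables, a different model and a wider interval. With 67 analysed per arm and SD 0.75, the 90%-power difference rises from about 0.42 to 0.46-0.54 at ICC 0.05 and 0.49-0.62 at ICC 0.10. The correction itself requires no extra participants, but with large groups and a high ICC, power at 0.54 would fall below 90%.
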